## Method

### Study design

This trial will adopt a multicenter, double-blinded, randomized controlled trial with two parallel groups, to explore the efficiency of the TJ methodology granules combined with PPI step-down for NERD. The protocol will be described in accordance with Recommendations for Interventional Trials 2013 guidelines [24]. The details of the study design are shown in Fig. 1.

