### Randomization and blinding

In this trial, center stratification will be used; each center will use the block randomization method, and qualified participants will be divided into intervention and control groups in a 1:1 ratio for grouping. Sequence generation is as follows: a table of random sampling numbers will be completed by an independent statistician through the PROC PLAN procedure in the Strategic Applications Software (SAS) V.9.2, and the results of the random allocation will be published through the network central random allocation system. The statistician will place the groups to be assigned into a double-layered, opaque envelope in sequence and seal the envelopes, and the clinical research coordinator will number the envelopes sequentially and maintain them. Allocation concealment mechanism is as follows: the person who generates the random sequence and decides on the allocation sequence should not be involved in the inclusion of participates and should not be involved in subsequent trials, especially in the measurement of outcomes. Prepare a list of assignment sequences, with each column containing the subject’s serial number, random number, drug name, or group identification. It is important that the serial number of each included subject corresponds to the random number generated in this order and that the order is not changed. Determine the group based on the random numbers. The participants’ sequence number and corresponding grouping will comprise the first-level blind code and, the medicine code will comprise the second-level blind code; each patient’s medicine code will be randomly assigned. Implementation is as follows: the designer, pharmacy, or statistician will each be provided with a copy of the distribution schedule, each sealed in an opaque envelope and kept under lock and key. The placebo used in the control group is treated to look, smell, and even taste similar to the drugs in the treatment group, making it difficult to distinguish. Participants, drug distribution center staff, and trial personnel were unable to determine the type of drug based on its appearance. Each participant will receive the corresponding medication according to their random code. All operations will be completed according to the established SOP guidelines. All codes will be kept in the Good Clinical Practice (GCP) Centre of Xiyuan Hospital. The TCM practitioners and statisticians administering the treatment will be blinded to the grouping.

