In the case of serious adverse events or complications in the clinical trials, blinding should be unsealed urgently, and cases of unblinding should be treated as dropout participates.

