### Outcomes and analysis

Participants in both the intervention group and control group will be encouraged to complete the treatment in 6 weeks, and follow-up will continue for 4 weeks. The following outcome indicators will be used to evaluate efficacy and safety. Demographic and clinical details of participants will be collected at the beginning of the trial. Physical safety examinations will be conducted at the beginning and end of the study, including (1) routine tests of blood, urine and stool, and fecal occult blood; (2) liver function tests (ALT, AST) and kidney function tests (Cr, BUN); and (3) electrocardiograms. Outcome indicators for efficacy evaluation will include the following: (1) a visual analog scale (VAS) for heartburn and regurgitation, (2) a major symptoms scale, (3) PPI withdrawal rate and symptoms recurrence rate, (4) a minor symptoms scale, (5) the MOS 36-item Short From Health Survey (SF-36), (6) the Patient-Reported Outcome (PRO) scale for chronic gastrointestinal diseases, (7) Self-Rating Anxiety Scale (SAS), (8) Self-Rating Depression Scale (SDS), (9) the Gastroesophageal Reflux Disease-Health-Related Quality-Of-Life (GERD-HRQL) scale, and (10) the TCM syndromes scale. Scales and questionnaires will be completed at the beginning and end of the trial and at the end of each phase and follow-up. Adverse events will be observed throughout the treatment.

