### Data management and monitoring

We will use both written and electronic CRF. At each time point, participants will complete the CRF under the guidance of a TCM physician. The completed CRF will be entered into the Drug & Clinical Trial Data Management Platform (developed by the GCP center: http://www.xyedc.com/). The CRF data will be entered in duplicate by two trained TCM physicians. Electronic data will be permanently saved. After the study, the statisticians will be able to download the electronic data for analysis through the platform.

The Data Monitoring Committee (DMC) reviews some of the data in the form of interim analyses to make preliminary judgments about the efficacy and safety of the study drug. The DMC is responsible for ensuring the safety and benefit of the subjects, the integrity and credibility of the trial, and the timely and accurate feedback of study results to the relevant areas of clinical research. The monitoring plan foresees the conduction of a total of four monitoring visits from the point of selection of the first study patients to the end of the regular monitoring visits. After charting all adverse events reported during the study period, the incidence of adverse events will be determined.

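### Any serious adverse event or undefined complication triggers urgent unblinding, whether or not the allocation is needed, and each unblinded case becomes a dropout

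*Protocol article*

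**What the plan says.** All references are to the protocol article.

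- **Design.** Study design commits to a double-blind trial: "This trial will adopt a multicenter, double-blinded, randomized controlled trial with two parallel groups".
- **Who is blinded.** Randomization and blinding says: "The TCM practitioners and statisticians administering the treatment will be blinded to the grouping". No exception is attached.
- **When the code is opened.** The same section ends with the rule "In the case of serious adverse events or complications in the clinical trials, blinding should be unsealed urgently".
- **What follows.** The sentence continues: "cases of unblinding should be treated as dropout participates".
- **Where the codes are.** "All codes will be kept in the Good Clinical Practice (GCP) Centre of Xiyuan Hospital". The section also mentions a network central allocation system, numbered envelopes maintained by the research coordinator, and sealed copies of the schedule.
- **Procedures elsewhere.** There is one general reference: "All operations will be completed according to the established SOP guidelines".
- **Safety data.** Outcomes and analysis says: "Adverse events will be observed throughout the treatment". Data management and monitoring adds that adverse event incidence will be determined, and that a monitoring committee sees interim data to "make preliminary judgments about the efficacy and safety of the study drug".

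**The concern.** In a double-blind trial, a participant's code is normally opened because someone caring for that participant needs to know the allocation. Here the occurrence of an event is enough. A serious event plainly unrelated to treatment, for which the arm would make no difference to care, would still lead to urgent opening. The second trigger, complications, has no definition or threshold, so two centres could apply it differently.

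Three things are at stake. First, codes are opened unnecessarily in a trial that relies on the blind. Second, each opening also removes a participant, so dropout is driven by safety events. Third, safety is a stated aim of the trial and serious events are a stated ground for early termination (Protocol amendments). If the arm is already known when such an event is assessed, that assessment is less secure than the double-blind label suggests.

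**Working it through.** The plan gives no figure on this point, so there is nothing to reproduce. The check is a reading of the rule against the other sections on blinding, dropout, adverse events, monitoring and analysis.

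**1. Is the trigger qualified anywhere?** Study design, Dropout criteria, Randomization and blinding, Outcomes and analysis, Data management and monitoring, and Statistical analysis were read for three things: a condition that the allocation be needed, a limit on who learns it, and a blinded assessment before opening. None contains any of these. The reference to standard procedures is general and does not mention code-breaking.

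**2. Does the rule fit the stated blinding?** The practitioner statement has no exception, while the unblinding rule applies to every triggering event and does not keep the result from the site. The two can be reconciled only by adding something the article does not say, such as a recipient outside the site team.

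**3. What happens to the participant?** The Dropout criteria section lists the participant's own decision, loss to follow-up, poor compliance, and a changed syndrome diagnosis or a physician's order to withdraw. Unblinding is not on that list. It becomes a dropout reason only through the unblinding sentence. So an unneeded opening creates a dropout that would not otherwise have occurred.

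**4. Is there a path to the safety assessment?** Opening is urgent, and no earlier recording of seriousness or relatedness is required. Assessment with the arm known is therefore possible for the triggering events. The article does not say that it happens.

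**5. Is there a path to the primary outcomes?** Unblinded cases are dropouts. Dropout criteria allows the last main efficacy value to be carried forward, and Statistical analysis allows carry-forward or multiple imputation. The carried value would normally predate the opening. The VAS comes from a daily diary card kept by the participant. No scheduled score after unblinding is described, so this path is weak.

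**6. How many participants?** No rate of serious events or complications is given. With an assumed proportion r, the count is 174 × r:

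| Assumed r | 174 × r |
|---|---|
| 0% | 0 |
| 1% | 1.74 |
| 2% | 3.5 |
| 10% | 17.4 |

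These proportions are assumptions that show scale only. What evidence the article has points to the low end: Background reports no adverse event in the team's earlier trial of the TJ granule, treatment lasts 6 weeks, and eligibility is limited to ages 18 to 65 without severe comorbidity. For comparison, the planned attrition allowance of about 20% is 174 × 0.20 = 34.8 participants for all reasons together.

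**The case against.** The strongest case for leaving the text alone has four parts.

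- **The wording can be read narrowly.** The adjective serious may govern both nouns, and urgency suggests an emergency procedure. This is a fair reading of complications. It does not supply the missing condition, because a serious event can still occur without any need to know the arm.
- **Detail belongs elsewhere.** Who decides, who sees the code and when relatedness is recorded are matters an article commonly leaves to the full protocol or to standard procedures. That stands, and their absence is not counted here as an error. The trigger and its dropout consequence, however, are stated outright.
- **The numbers may be tiny.** This stands. The size is unknown and could be zero.
- **Narrowing a safety rule has a price.** Delayed access in an emergency would be a real cost, so the rewording must keep emergency access at every centre.

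A reader might also infer stronger points that the article does not support:

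- **Harms in general are judged with the arm known.** No relatedness rating, assessor or recipient of the code is described, and non-serious events stay blinded unless they are read as complications.
- **The primary scores are biased.** The dropout clause largely closes that path.
- **Opened codes reveal the next assignments.** Block size is not disclosed, and each participant's medicine code is randomly assigned under a two-level blind.
- **Five of the six hospitals cannot open a code in time.** Codes are held at one centre, but envelopes and sealed copies are also described, and the article does not say which route is used in an emergency.

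**Conclusion.** The point holds for the rule as written. The event alone opens the code, no need for the allocation is required, complications are undefined, and each opening creates a dropout. This conflicts with the unqualified blinding of practitioners in the same section. It is a badly fixed rule, not missing detail.

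That serious events may be assessed with the arm known is a reasonable inference, resting on urgent opening and no described prior assessment. It is not something the article states. The effect is unquantified and probably falls on few participants, and no direct effect on the primary result is shown. The conclusion does not depend on any assumed event rate. The change is worth making because it prevents avoidable unblinding and avoidable dropout at almost no cost.

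**What to change.** Reword the closing rule of Randomization and blinding to say:

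- An individual participant's code is opened only when knowledge of the allocation is needed for that participant's care, with emergency access kept for all six centres.
- For other serious events, the blind is kept at the site.
- Seriousness and relatedness are recorded before any code is opened, where time allows.
- Openings are made one participant at a time and logged, through whichever existing code-holding route supports this. The article says only that allocation results are published through the network system, so its ability to open single codes must be confirmed before it is named.
- The word complications is either defined or removed, since the need for the allocation becomes the test.

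The cost is a wording change, a log, and confirmation of the access route, with ethics re-approval as the article requires for any protocol modification. The small downside is that some events stay blinded until analysis. No dose or treatment rule is affected.

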#### Dropout criteria

Decision to exit the trial himself/herselfLoss to follow-upPoor complianceDiagnosis with other TCM syndromes or an order to withdraw by the TCM physicians

For the occurrence of patients presented with the above situation, we will consider making a suspension. In cases of dropout, the reason should be explained. If there are baseline pharmacodynamic data, the last main therapeutic effect index can be transferred to the final results for statistical analysis, and the CRF should be retained.

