**Assessment**										
VAS of heartburn and reflux		○	○	○	○	○	○	○	○	○
Major symptoms scale		○	○	○	○	○	○	○	○	○
Minor symptoms scale		○	○	○	○	○	○	○	○	○
TCM syndromes scale		○		○		○		○	○	○
SF-36		○		○		○		○	○	○
PRO for chronic gastrointestinal diseases		○		○		○		○	○	○
SAS		○		○		○		○	○	○
SDS		○		○		○		○	○	○
GERD-HRQL		○		○		○		○	○	○
Compliance			○	○	○	○	○	○		
Cointerventions			○	○	○	○	○	○		
Adverse events			○	○	○	○	○	○		

*VAS* visual analog scale, *TCM* traditional Chinese medicine, *SF-36* the MOS 36-item Short From Health Survey, *PRO* Patient-Reported Outcome, *SAS* Self-Rating Anxiety Scale, *SDS* Self-Rating Depression Scale, *GERD-HRQL* the Gastroesophageal Reflux Disease-Health-Related Quality-Of-Life

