### Compliance

The patient’s compliance will be calculated as “actual dose/dose to be taken”; if the compliance is in the range of 0.7 to 1.2, it will be regarded as good compliance. Participants should return unused medicine and empty packaging at each visit, and TCM physicians will count the number of drugs and granules returned and keep a record of lost and unreturned medicines.

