### Statistical analysis

This trial will use intention-to-treat (ITT) analysis as the main method to evaluate the outcome results. To deal with missing outcome variables that remain to be recorded, the last record data will be carried over to the end or a multiple imputation method will be used.

Statistical analysis will be conducted using the SPSS 21.0 software. The significance level is established at 0.05, and the limits of the confidence interval are 95%. Descriptive analysis and categorical variables will be described in frequency tables and as percentages or composition ratios; continuous variables will be described in terms of means and standard deviations (SDs), or medians, lower quartiles (P25), upper quartiles (P75), minimum values, and maximum values. Comparative analyses between two groups will be performed for categorical variables using the chi-squared test, Fisher’s exact probability method, the Wilcoxon rank-sum test, or the CMH test. Continuous variables that conform to a normal distribution will be compares using a *t*-test (for homogeneity of variance between groups, with 0.05 as the test level; if the variance is heterogeneous, the Welch-Satterthwaite *t*-test will be used), while those that conform to a non-normal distribution will be compared using the Wilcoxon rank-sum test or the Wilcoxon signed-rank test. Hypothesis testing will use the two-sided test uniformly, and *P* ≤ 0.05 will be considered statistically significant.

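### Participants unblinded after a serious adverse event, poorly compliant or re-diagnosed are classed as dropouts, so their later outcomes may go unobserved and be filled in, which fits poorly with ITT; Table 1 and the text also disagree on safety assessments

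*Protocol article*

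**What the plan says.** **Dropout and analysis.** Under Randomization and blinding, when a serious adverse event or complication occurs, "blinding should be unsealed urgently, and cases of unblinding should be treated as dropout participates". The Dropout criteria also list poor compliance and diagnosis with another TCM syndrome. The Compliance section defines the good range: "if the compliance is in the range of 0.7 to 1.2, it will be regarded as good compliance". For a dropout with baseline data, "the last main therapeutic effect index can be transferred to the final results for statistical analysis, and the CRF should be retained". Statistical analysis states: "This trial will use intention-to-treat (ITT) analysis as the main method to evaluate the outcome results". For missing outcomes, "the last record data will be carried over to the end or a multiple imputation method will be used".

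**Safety assessments.** Outcomes and analysis states: "Physical safety examinations will be conducted at the beginning and end of the study". Table 1 marks that examination in the screening column only. The same section says: "Adverse events will be observed throughout the treatment". The Table 1 row "Adverse events" is ticked at weeks 1 to 6 and blank at weeks 8 and 10. Data management and monitoring, however, determines incidence from all events reported over the study period, and Timeline sets a trial of 10 weeks.

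**Allergy.** One item of the Exclusion criteria covers allergies that arise while the trial is running.

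**The concern.** Unblinding for a serious adverse event, poor compliance and a changed syndrome diagnosis all occur after randomisation, and assigned treatment can influence each of them. Two of the three are classifications made by the trial team, not withdrawals by the patient. If such a classification ends observation, the ITT result rests on filled-in values for the participants in whom treatment went least according to plan, possibly unequally between arms.

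Safety is a stated aim in the Background. A site that works from Table 1 would not schedule the closing blood, liver, kidney and ECG tests that the text requires. It would also have no scheduled adverse-event recording in the last four weeks.

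**Working it through.** **1. What happens to a dropout's data.** Side by side:

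- The Dropout criteria say a suspension will be considered. They allow the last efficacy value to be used, provided baseline data exist. The wording is permissive and conditional.
- Statistical analysis makes ITT the main method, with carry-forward or multiple imputation, and does not choose between them.
- No section says that a dropout is excluded from analysis. No section says that a dropout continues scheduled assessments.

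Inclusion is therefore possible but not secured, and continued observation is not stated.

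**2. Effect of carry-forward on the responder endpoint.** Inputs from Primary outcomes: a responder has a weekly VAS reduction from baseline of at least 50% in at least 50% of the 6 weeks. The threshold is 0.5 × 6 = 3 weeks.

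Assume that the weekly VAS value is what is carried forward, that the last recorded week is week *k*, and that week *k* meets the 50% reduction. The remaining 6 − *k* weeks then inherit it, so the count of qualifying weeks is at least 1 + (6 − *k*) = 7 − *k*.

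| Last recorded week *k* | Filled weeks | Minimum qualifying weeks | Responder whatever came before? |
|---|---|---|---|
| 1 | 5 | 6 | yes |
| 2 | 4 | 5 | yes |
| 3 | 3 | 4 | yes |
| 4 | 2 | 3 | yes |
| 5 | 1 | 2 | no, one earlier week needed |

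Example: a participant meets the reduction in week 1, then has a serious adverse event, is unblinded and becomes a dropout. Carry-forward gives 6 of 6 qualifying weeks, a responder. If weeks 2 to 6 had been observed and none qualified, the count would be 1 of 6, a non-responder.

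The rule also works the other way. If the last recorded week does not qualify, all filled weeks fail, and anyone leaving by week 3 is a non-responder. The direction of the net bias between arms cannot be read from the documents.

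**3. Size per case.** One misclassified participant in an arm of 87 changes its responder rate by 1/87 = 1.1 percentage points. The Sample size section plans on 90% against 70%, a difference of 20 points. This is a conversion factor only. The documents give no rate of serious adverse events, unblinding, poor compliance or re-diagnosis.

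**4. Safety schedule.**

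| Item | Text | Table 1 |
|---|---|---|
| Physical safety examination | beginning and end of study | screening only |
| Adverse-event observation | throughout treatment (6 weeks) | weeks 1 to 6 |
| Adverse-event incidence | events over the study period (10 weeks in all) | weeks 8 and 10 blank |

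The first row is a contradiction. In the second, text and table agree with each other. The third does not fit them: 10 − 6 = 4 weeks fall in the study period without scheduled recording, although visits exist at weeks 8 and 10.

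**5. Allergy.** An exclusion criterion is applied before enrolment. An allergy that appears later is a post-enrolment event, and the item does not say how it relates to adverse-event reporting.

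**The case against.** A reader might infer that the worst cases are lost to both the ITT and the safety analysis. The documents do not support that. Dropouts are not excluded anywhere. Their last value may be used or imputed, their case report forms are kept, and incidence counts all reported adverse events with no exception for unblinded cases. Suspension is only to be considered. Definitions of analysis sets are commonly left to a fuller document that is not shown.

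A reader might also infer that laboratory toxicity would go unseen. The text does plan closing tests; the omission is in the table, and it would bite only where a site followed the table alone.

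The adverse-event window is mostly consistent, since Table 1 and Outcomes and analysis both limit observation to treatment. Only the study-period wording in Data management and monitoring pulls against them.

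A reader might size the problem by the 20% attrition allowance, 87 × 0.20 = 17.4 per arm. That is an allowance for losses of every cause and says nothing about how many arise from these rules. The Background reports no adverse event in the team's earlier trial, so unblinding for harm may be rare.

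All of this stands and limits the claim. It does not answer the central point: retaining a dropout by carry-forward is not the same as observing the participant, and step 2 shows that it can record a harm-related exit as a success.

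**Conclusion.** The point holds in a limited form. Classing participants as dropouts for unblinding, poor compliance or a changed syndrome fits poorly with ITT as the main analysis, because their later outcomes may not be observed and may be replaced by a carried-forward value. Under that option a single qualifying last week, at week 4 or earlier, is enough for responder status. This rests on two assumptions: that carry-forward, not multiple imputation, is used, and that it acts on the weekly VAS score. The number of participants affected and the direction of the bias are unknown.

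Table 1 contradicts the text on the closing safety examination. The adverse-event window and the period for computing incidence need to be reconciled, as does the allergy wording. These changes should be made, but they do not show that the trial's analysis excludes harms.

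**What to change.** 1. In Randomization and blinding and in the Dropout criteria, state that participants who are unblinded, poorly compliant or re-diagnosed stay in the ITT and safety sets in their randomised arm. State that they continue scheduled outcome and safety assessments unless they withdraw consent, whether or not they remain on study treatment. This concerns follow-up and analysis only and sets no rule on treatment.
2. Add the end-of-study physical safety examination to Table 1 and name the visit, since end of study could mean week 6 or week 10.
3. Reconcile the adverse-event window with the period used for incidence, most simply by recording adverse events at the existing week 8 and week 10 visits.
4. Reconcile the exclusion item on allergies arising during the trial with adverse-event reporting.

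The cost is a few sentences and some Table 1 ticks. The visits exist and the closing tests are already promised in the text. The added burden is continued assessment of participants who would otherwise have stopped.
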